### Data analysis

To analyze the recall and transmission of information provided by each model in the texts, we consider the central propositions recalled and transmitted by the participants in each of the conditions presented in the texts. Central propositions are the key points of information in a narrative. In our texts, there are seven propositions for each model presented in each of the stories.

Each proposition was identified by its central subject (Table 2), which enabled the identification of the central propositions that were most commonly remembered by the volunteers and the models to which they belonged.

To determine which information is most likely to be remembered and transmitted, we will consider each proposition as a binary result (whether the participant remembered it or not). We will then perform a multilevel logistic regression, considering the participant as a random effect and as a fixed effect: Hypotheses 1 and 2—type of model (digital influencer, physician, politician, and family member). To test the validity of the statistical models, they will be compared with a null model (which will only consider the effect of grouping by participants using the X^2^; test for model adjustments, through the ANOVA function, and the maximum likelihood estimate. The tests will be performed in an R environment [32] using the package lme4 [33].

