### Transmission stage

The second experiment to be carried out aims to test the hypothesis referring to the transmission of information related to COVID-19: specifically, on whether the presence of a prestigious role model favors the transmission of information over successive generations. Similar to the first experiment, this one will be carried out online, through a platform specifically developed for research of this nature, by the Laboratory of Ecology and Evolution of Socioecological Systems at the Federal University of Pernambuco.

A linear transmission chain experiment will be carried out, a method originally developed by Bartlett [29], which has been used in studies of cultural evolution over the years. It allows for the simulation of information transmission along a chain of individuals and occurs as follows: the first participant in the chain reads the material and, after a distraction task, is asked to recall the material read. In the original method, the resulting recall is then passed to the second participant, who does the same, and this continues along the chain (Fig 3). We will test 16 chains of four participants (representing four generations) for each proposed condition, totaling 64 chains.

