**Fig 3 pone.0281991.g003:**
[figure not shown]
Representation of a linear chain transmission study [30].

The initial phase of this experiment will be similar to the first experiment, from clicking on the research link right up until the surprise recall test.

Following this, the experiments differ because, after this recall activity, the participant will receive a further instruction: “*Now*, *please transmit the information you obtained from the reading material to someone else by writing it here*. *You have 10 minutes to complete this activity*.” This transmission activity was conceived with the idea of testing whether what the person remembers at first is what they transmit when requested (Fig 4). At the end of this activity, a self-reporting step will take place followed by a message of acknowledgement and appreciation before being removed from the platform. The product of the information recall will undergo a spelling and grammar check, carried out by the researcher the information will then be directed to the next participant in the chain (corresponding to the 2nd generation). This entire process is repeated until the fourth and final participant in the chain is reached.

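### In the transmission chains, the stated scoring rule and participant-only model count carried-forward omissions as independent failures, so the Hypothesis 1 test rejects too often

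*Protocol article*

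**What the plan says.** The Data analysis section of the protocol article covers recall and transmission together. Its stated purpose is "To determine which information is most likely to be remembered and transmitted", and the outcome is defined once: "we will consider each proposition as a binary result (whether the participant remembered it or not". The propositions are those of the stories as written (Table 2): "In our texts, there are seven propositions for each model presented in each of the stories".

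One multilevel logistic regression serves both hypotheses, "considering the participant as a random effect and as a fixed effect" the "type of model (digital influencer, physician, politician, and family member". It is compared by chi-square with a null model "which will only consider the effect of grouping by participants". There is no chain term, no generation term and no term for what a participant was given to read.

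The Transmission stage section describes the chain method: "the resulting recall is then passed to the second participant, who does the same, and this continues along the chain". In this trial the researcher corrects the spelling and grammar of the recall product and sends it to the next person. "This entire process is repeated until the fourth and final participant in the chain is reached". Only the first of the four members therefore reads the full story.

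**The concern.** The rule suits the recall stage, where everyone reads all seven propositions. In a chain, whether a participant remembered a proposition has no clear meaning if that participant never received it. Scored against the story, each early omission is repeated as a zero for every later member.

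The participant intercept does not deal with this. It allows for differences between people, but it takes the four members of a chain to be independent of one another, when their scores are linked through the shrinking text. At stake are the error rate of the only stated test of Hypothesis 1 and the meaning of its odds ratio.

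**Working it through.** **The plan's own figure.** The Sample size section gives 327 (odds ratio 1.81, base rate 0.1, alpha 0.05, power 0.95, R² = 0, z = 1.64). The Demidenko formula with variance correction, one-sided, with a standard normal covariate gives 326.2, rounded up to 327, so the figure reproduces. For the chains, 327/16 = 20.4, rounded up to 21 per text, and 21 × 4 × 4 = 336. The calculation assumes independent observations, so it makes no allowance for chains.

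**A worked chain.** Person 1 recalls 4 of 7, and persons 2 to 4 each recall all 4 propositions they received. The rule scores 4/7 = 57% for each of the four. Person 1's three omissions become 3 × 4 = 12 zeros, of which 3 × 3 = 9 belong to people who were never shown the proposition.

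**Expected share.** Let r be the chance that a proposition received is retained (an assumption). Then P(present after generation g) = r^g and P(never shown at generation g) = 1 − r^(g−1). At r = 0.6 the never-shown shares for generations 1 to 4 are 0, 0.400, 0.640 and 0.784, which sum to 1.824. That is 1.824/4 = 46% of all scores and 1.824/3 = 61% of scores in generations 2 to 4. All zeros average (0.400 + 0.640 + 0.784 + 0.870)/4 = 0.674, so 0.456/0.674 = 68% of zeros are carried forward.

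| r | never shown, all scores | never shown, generations 2–4 | share of zeros carried forward |
|---|---|---|---|
| 0.5 | 53% | 71% | 69% |
| 0.6 | 46% | 61% | 68% |
| 0.7 | 37% | 49% | 66% |
| 0.8 | 26% | 35% | 64% |
| 0.9 | 14% | 19% | 62% |

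**Rejection rate with no role-model effect.** Each simulated trial had four texts, 16 or 21 chains of four per text and seven propositions. The model was the planned one, with a likelihood ratio test on 3 df at 5%. The text scored was taken to be the text passed on, lost propositions did not return, and chain members shared nothing except their omissions. SD is the assumed between-participant SD on the logit scale. There were 200 to 400 runs per row; with 400 runs the Monte Carlo standard error is about 1 to 2.5 points.

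| chains per text | r | SD | all seven scored | only received propositions scored |
|---|---|---|---|---|
| 16 | 0.6 | 0 | 10% | 6% |
| 16 | 0.6 | 0.5 | 12% | 6% |
| 16 | 0.6 | 0.7 | 18% | 5% |
| 16 | 0.75 | 0.5 | 20% | 5% |
| 16 | 0.75 | 0.7 | 19% | 6% |
| 16 | 0.9 | 0.5 | 37% | 6% |
| 21 | 0.6 | 0.5 | 13% | 6% |
| 21 | 0.6 | 0.7 | 12% | 3% |
| 21 | 0.75 | 0.5 | 22% | 5% |
| 21 | 0.9 | 0.5 | 37% | 6% |

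At SD 0.5 the rate hardly changes between 16 and 21 chains, so more chains do not cure it.

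**Keeping all seven but handling the chain** (16 chains, SD 0.7, r = 0.6 and 0.75, 200 runs). Rejection is 12.5% and 22.5% as written. It is 5.0% and 4.5% with a chain intercept and generation, and 2.5% and 4.0% with one value per chain.

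**Estimate** (true per-step odds ratio 1.81, 16 chains, SD 0.7). At r = 0.6 and 0.75 the median is 2.18 and 2.03 with all seven scored, and 1.86 and 1.83 with only received propositions scored. In a separate set of 142 to 157 runs per setting, all-seven scoring with a chain intercept and generation gave 2.20 and 2.11.

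**The case against.** The strongest reply is that scoring against the full story is not a mistake. The Transmission stage section asks whether a prestigious source helps information pass along a sequence of generations, and that is cumulative survival. In the worked chain, 4/7 is the correct survival figure at every generation. This stands. So does its consequence: once the chain is handled, all-seven scoring gives a correctly sized test. The error is the pairing of that score with a model that ignores the chain.

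A reader might infer three stronger things that the article does not support:

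- **That the rule is biased against some role model.** All four texts are scored alike, and median odds ratios under no effect were 0.96 to 1.07.
- **That the odds ratio is simply inflated.** The gap between 2.0–2.2 and 1.81 compares a cumulative effect with a per-step effect. The fault is that the plan does not say which it means.
- **That the article expressly scores later generations on all seven.** It does not say so. It defines the propositions by the story, sets one rule for both stages and nowhere limits scoring to what was received, so this is the plain reading only.

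Two further cautions stand. Re-emergence is possible: the Table 2 items on supporting the drug and on Postex being used overlap, so a later reader could restate one from the other. And scoring only received propositions conditions on what survived after randomisation. When propositions differed in memorability (SD 1 on the logit scale, r = 0.6, true odds ratio 1.81, 100 runs), that method gave a median odds ratio of 1.58 and 50% rejection; part of the shift is non-collapsibility.

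The reply that coding detail belongs in a fuller plan does not dispose of the point. The article states a rule and a model, and together they do not fit the chain design.

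**Conclusion.** The concern holds in this form: on its plain reading, the Data analysis section enters carried-forward omissions as independent failures of separate participants. The nominal 5% test of Hypothesis 1 then rejects a true null in roughly 10% to 37% of trials, and its odds ratio blends cumulative survival with per-person recall.

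The size rests on assumed retention of 0.6 to 0.9, participant SD of 0 to 0.7, equally memorable propositions and no re-emergence. The direction was the same in every setting run. The article gives 8 (Abstract), 16 (Transmission stage) and 21 (Sample size) chains per text; the last two were simulated and 8 was not. The recall stage is unaffected.

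**What to change.** Leave the recall-stage rule as it is. For the transmission stage, state in Data analysis which quantity is estimated and match the analysis to it:

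- **(a) Cumulative survival**, which fits the aim in the Transmission stage section. Score every generation against all seven propositions and analyse by chain: either one value per chain, such as the number of propositions still present at generation 4, or the mixed model with a chain random effect and generation added.
- **(b) Per-person transmission.** Score generation 1 on all seven. Score generations 2 to 4 only on propositions present in the corrected text that the participant received, and treat the rest as not applicable. Fit the mixed model to those records with a proposition effect, and add a rule for propositions that re-emerge.

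Make one primary and report the other as supportive.

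No new data are needed, since the forwarded text is already coded for propositions. The costs are these:

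- **Power.** At a true per-step odds ratio of 1.81 with 16 chains and SD 0.7, rejection falls from 89–93% with the oversized test to 73–77% under (b). In the separate set of runs, the chain-and-generation form of (a) gave 67–68%, against 74–75% under (b).
- **Records.** Option (b) drops the never-shown records, 14% to 53% of the nominal total for r from 0.9 to 0.5.
- **Interpretation.** Option (b) carries the post-randomisation conditioning described above.

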### Sample size

Individuals aged 18 years and older with access to the Internet will be selected to participate in the research. The recruitment of volunteers will be carried out through the dissemination of the survey on social networks such as Instagram, Twitter, Facebook, WhatsApp, and E-mail. To determine the sample size for the recall stage, we used the G*Power 3.1.9.7 software [25]. We conducted an *a priori* analysis to determine both the sample size and its power. As a basis for the study, we took the effect size (Odds ratio = 1.81) in a study by Bonin et al. [26] as it is the most recent study that brings memory-related variables and employs the same statistical test that we propose to use. We calculated a sample size of 327 people with an explanatory power of 95% and z = 1.64. The default for Pr(y = 1|x = 1)H0 in the G*Power software is 0.2 (i.e., a 20% probability of the event occurring if the null hypothesis is true). However, we use 0.1 to obtain an even more reliable sample size for the phenomenon we are investigating. We consider an α of 0.05, a Power (1-β err prob) of 0.95, R^2^; = 0, and normal distribution. Fig 1 presents the parameters used for this calculation.

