**Fig 1 pone.0281991.g001:**
[figure not shown]
Parameters used to calculate the sample size based on a power analysis.

The calculation for the transmission stage was based on the same parameters. However, as this stage will be conducted in transmission chains of four people each, we divided the total number of 327 people by 4 and rounded the result to the nearest whole number, arriving at a total of 21 chains per text used and 336 participants (an increase of 9 people from the calculated sample).

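### The transmission-stage (H1) model has no chain effect although chain members are dependent by design, so its role-model test is too liberal and the 95% power does not carry over

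*Protocol article*

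**What the plan says.** The Data analysis section scores each of seven central propositions as present or absent and gives one model for Hypotheses 1 and 2: "We will then perform a multilevel logistic regression, considering the participant as a random effect and as a fixed effect", the four-level type of role model. This is compared by a chi-square test with a null model whose only grouping is the participant, using lme4. Neither chain nor generation appears in either model.

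The Transmission stage section describes linear chains of four people. Each person's recall, after a spelling and grammar check, becomes the next person's reading material. The aim is to test "whether the presence of a prestigious role model favors the transmission of information over successive generations". The prediction under Hypothesis 1 is simpler: information attributed to the prestigious source is transmitted more often than the same information attributed to the other three.

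The Sample size section reports: "We calculated a sample size of 327 people with an explanatory power of 95% and z = 1.64". For the transmission stage it reuses this number: "we divided the total number of 327 people by 4 and rounded the result to the nearest whole number", giving 21 chains per text and 336 participants. The Transmission stage section says 16 chains per condition (64 in all), and the Abstract says eight per story.

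**The concern.** A participant intercept accounts for the correlation among the seven propositions scored for one person. It does nothing for the correlation between people in the same chain. If the first member drops a proposition, the text the second member reads does not contain it, and the loss tends to pass down the chain. What varies independently is therefore the chain, while the planned model treats all four members as independent replicates of the role-model condition.

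H1 is one of the study's two hypotheses. Its test would declare a role-model difference too often when there is none, and its intervals would be too narrow. The planned size of the transmission stage rests on the same assumption of independent people.

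**Working it through.** **1. The plan's own figure.** Inputs from the Sample size section: one-sided α 0.05 (implied by z = 1.64), power 0.95, odds ratio 1.81, base probability 0.1, R² = 0, a normally distributed covariate. The logistic-regression Wald formula is

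N = (z₁₋α·√v₀ + z₁₋β·√v₁)² / (ln OR)²

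Here ln 1.81 = 0.593 and both z values are 1.645. The mean event probability over the covariate is 0.1125, so v₀ = 1/(0.1125 × 0.8875) = 10.02. From the inverse information matrix, v₁ = 11.22. Then N = (1.645 × (3.165 + 3.350))² / 0.352 = 326.2, rounded up to 327. The stated figure is reproduced, and it contains no clustering term. For the chains, 327/4 = 81.75; over four texts this becomes 21 chains each, and 21 × 4 × 4 = 336.

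**2. Design effect.** With four people per chain, DE = 1 + 3 × ICC. If the model ignores the chain, the actual error of the 3-df test is about P(χ²₃ > 7.815/DE). The protocol gives no ICC, so the values below are assumed.

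| ICC | DE | Actual error at nominal 5% | 336 people are worth |
|---|---|---|---|
| 0.05 | 1.15 | 7.9% | 292 |
| 0.10 | 1.30 | 11.1% | 258 |
| 0.20 | 1.60 | 18.0% | 210 |
| 0.30 | 1.90 | 25.0% | 177 |
| 0.45 | 2.35 | 34.4% | 143 |

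**3. Simulation of the planned test.** Assumptions: no source effect, 21 chains per condition, seven propositions, a proposition passed on only if present in the text read, 400 runs per setting.

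| Retention per step | Participant SD (logit) | Rejection at nominal 5% |
|---|---|---|
| 0.50 | 0.5 | 11% |
| 0.50 | 1 | 15% |
| 0.70 | 0.5 | 20% |
| 0.70 | 1 | 28% |
| 0.85 | 0.5 | 26% |
| 0.85 | 1 | 34% |

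The design effect in these runs was 1.19 to 2.29, an ICC of (1.19 − 1)/3 = 0.06 to (2.29 − 1)/3 = 0.43.

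**4. Checks on the cause.**
- With an ordinary random chain effect instead of strict inheritance, the planned test rejects 9 to 10% when 10% of the person-level variance lies between chains, and about 30% when half does. With no chain variance it rejects 4 to 6%. The inflation therefore comes from the chain.
- Analysing chain means in inheritance simulations with 8, 16 or 21 chains per condition gives 4.6 to 5.3%. A mixed model with chain and generation gave about 6% in runs of 149 to 199 simulations, where the Monte Carlo error is close to 2 points.
- Allowing lost propositions to return, an analysis of variance of participant scores (a stand-in for the planned test) rejects about 10 to 29% with 10 to 30% reintroduction. The same kind of check over 16 or 21 chains, including 20% reintroduction, spans about 7 to 32%.
- The inflation is nearly the same with 8, 16 or 21 chains per condition.

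**5. Effective size under each stated chain count.**

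| Chains per condition | People | Worth at ICC 0.1 (÷1.3) | Worth at ICC 0.3 (÷1.9) |
|---|---|---|---|
| 21 | 336 | 258 | 177 |
| 16 | 256 | 197 | 135 |
| 8 | 128 | 98 | 67 |

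**The case against.** Several stronger readings are tempting, and the document does not support them.

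- **A known false-positive rate.** No rate can be read off the plan. The protocol gives neither retention nor a within-chain correlation, so the range depends on the assumed values. H1 may also be scored on the separate transmission text, whereas the recall text is what is passed on. The simulation uses one output per person, so the size of the dependence for the transmission text is untested.
- **Lost propositions can never return.** This is too absolute. Propositions 2 (support for the drug) and 7 (that it should be used) overlap, so a reader could rebuild one from the other. Allowing for this lowers the top of the range but leaves clear inflation.
- **The missing generation term inflates the error.** It does not in a balanced design. It adds generation differences to the participant variance and leaves change along the chain unmodelled.
- **H1 must be tested on source by generation.** The stated prediction is a main effect of source. A second route to declaring H1 supported would itself need a multiplicity rule.
- **A specific reduced power.** The 327 comes from a one-sided formula with a normal covariate and one outcome per person. The planned test has 3 degrees of freedom on a four-level factor with seven outcomes per person. Putting a smaller effective number through that formula does not give the power of the planned test.

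It could also be said that a journal article leaves such detail to an analysis plan. That does not apply here, because the article names the random effect, the fixed effect and the null model.

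**Conclusion.** The point holds for H1. The model and its null are stated explicitly, and they omit the level at which the transmission data are dependent. Rejection with no source effect is roughly 7 to 35% at a nominal 5%, assuming per-step retention of 0.5 to 0.85 and a participant SD of 0.5 to 1 logit (implied ICC about 0.05 to 0.45). The direction is secure and survives partial reappearance of lost propositions. The exact size is not known.

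The 95% power does not carry over to the transmission stage, and the loss of information depends on the ICC and on which of the three chain counts is used. The aim of following transmission over successive generations is left unmodelled, which is a separate gap and not a cause of the inflation. H2, tested in the recall stage, has no chains and is unaffected.

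**What to change.** 1. For H1, replace the shared model by `y ~ source + generation + (1|chain) + (1|chain:participant)`. The null model keeps both random intercepts and the generation term and drops only source.
2. Test H1 on the source effect alone. Report source by generation as a secondary analysis that addresses the aim of following transmission along the chain.
3. State that the chain is the independent unit in the transmission stage and that the 95% power was calculated for independent people.
4. Restate the transmission-stage power for the planned test, using DE = 1 + 3 × ICC over a stated ICC range.
5. Settle one chain count in place of the 8, 16 and 21 now given in the Abstract, Transmission stage and Sample size sections, and base the restated power on it.

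The model needs no additional data items, only a record of each participant's chain and position. The price is wider intervals and a less favourable power figure, and possibly more chains if that figure is judged too low. The recall-stage analysis needs no change on this account.

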## Hypotheses

**Hypothesis 1**: The transmission of information related to COVID-19 is strongly influenced by a source who possesses prestige.

*Prediction*: Information related to COVID-19 that is attributed to someone with prestige (digital influencers) is transmitted more often than the same information attributed to political role models, role models with public health expertise, and family members.

According to Henrich and Gil-White’s [12] theory, prestige is based on the merit that other people confer on certain individuals, which promotes greater admiration from others and a desire to be close. The "status" involved in this is proportional to the amount of attention received. Thus, as an individual receives more attention, their status will be higher [10]. The assumptions of the theory are as follows: [i] qualified individuals have a higher status; [ii] older individuals tend to obtain more prestige than younger individuals; [iii] individuals with perceived skill/knowledge receive privileges and are exempted from certain social obligations; [iv] people preferentially mirror qualified/successful individuals; [v] prestigious individuals are influential even beyond their domain of expertise; and [vi] prestigious individuals are more memorable.

Jimenez and Mesoudi [13] gathered existing evidence in the literature on prestige bias and added to their initial predictions, including the following: [i] prestigious individuals tend to be successful in domains that are currently important to a social group or that were valued in the recent past; [ii] prestigious individuals only achieve social influence when their domain of prestige is currently valued by a social group; [iii] the positive association between perceived success and prestige will be greater than the positive association between actual success and prestige; [iv] a more positive correlation between prestige and success indicates that more people will employ social learning with prestige bias; [v] prestigious individuals will be mirrored more often when the variation in knowledge/skill within a group is larger; [vi] prestige bias across domains occur more often when cues are not as evident within the domain tested than when those cues are clear; [vii] prestige bias across domains occur when there are general traits, which make people successful across domains [13].

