Prestige bias allows individuals to acquire information quickly and is less costly in a new environment, thus increasing the chances of acquiring potentially more adaptive information [12]. Atkisson et al. [22] investigated this through an experiment in which participants designed arrowheads and tried to maximize hunting success; this was measured in caloric return. Their main findings revealed that participants learned preferentially from prestige models, defined as models that others spent more time looking at, and that prestige information and success-related information were used to the same degree. Thus, their results support the important role that prestige bias plays in social learning [22].

Moya et al. [1] noted that in a context such as the COVID-19 pandemic, in which epidemiological and social changes were rapid and abrupt, the source transmitting information can exert great influence on the information that people will reproduce. Recent evidence shows us that the existence of social bubbles on social media platforms such as Twitter allows for false and true information about COVID-19 to be shared in the same proportion; additionally, this conformity may be associated with ideological issues and the person transmitting the information [9]. In light of this information and the theory of the evolution of prestige, we believe that people will select sources with social prestige to reproduce and transmit information about COVID-19.

**Hypothesis 2**: Recall of information related to COVID-19 is strongly influenced by a source that possesses social prestige.

*Prediction*: Information related to COVID-19 attributed to someone of prestige (digital influencers) is transmitted more often than the same information attributed to political role models, role models with public health expertise, and family members.

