### Elaboration of the texts

The texts will contain a brief contextualization of the pandemic scenario; then, a particular opinion about the use of the drug Postex in the treatment of COVID-19 will be reported and attributed to one of the role models. By attributing the opinion to the role models, we will describe the characteristics that may confer prestige onto them. In this way, we will be able to determine whether the prestigious role model influences the retention and transmission of information. The stories have approximately the same number of words, ranging from 123 to 129 (S1 File).

All texts have the same structure; first, the pandemic context; next, a model with an opinion on the use of the medication. The number of central propositions referring to each of the models is also equal (Table 2).

**Table 2 pone.0281991.t002:** Central propositions used in the story texts for the experiments on recall and transmission of information about COVID-19.

Central Propositions	
Contextualization	Pandemic context
Proposition 1	Characterization of the role model
Proposition 2	Support for use of the drug
Proposition 3	Decrease in the number of deaths
Proposition 4	Decrease in the number of hospitalizations
Proposition 5	Assertion that use is safe
Proposition 6	Success rates exceed failure rates
Proposition 7	Postex should be used

All texts will be randomized so that they have the same chance of being assigned to participants.

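### The only test the analysis names is undirected across the four role models and, taken alone, does not address the prediction that the influencer exceeds each of the other three

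*Protocol article*

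**What the plan says.** In the Protocol article, Hypotheses, the prediction for Hypothesis 1 is that influencer-attributed information "is transmitted more often than the same information attributed to political role models, role models with public health expertise, and family members". The prediction for Hypothesis 2 has the same form: "Information related to COVID-19 attributed to someone of prestige (digital influencers) is transmitted more often than the same information attributed to political role models", and goes on to the other two sources. (It speaks of transmission although Hypothesis 2 concerns recall; I read it as recall.) Each prediction is therefore directional and names three comparators.

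Under Data analysis, each proposition is scored as a binary outcome, and "there are seven propositions for each model presented in each of the stories". The regression has a random participant effect and one fixed effect, "type of model (digital influencer, physician, politician, and family member". The section then says "To test the validity of the statistical models, they will be compared with a null model", using a chi-square "test for model adjustments, through the ANOVA function, and the maximum likelihood estimate". It names no reference level, contrast, direction or rule for combining three comparisons.

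Under Sample size, the figure of 327 rests on an odds ratio of 1.81, z = 1.64, a normally distributed predictor and an outcome probability of 0.1: "We consider an α of 0.05, a Power (1-β err prob) of 0.95". On allocation, Elaboration of the texts says "All texts will be randomized so that they have the same chance of being assigned to participants".

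**The concern.** The predictions and the named test ask different questions. The predictions ask whether one particular source exceeds each of three others. The test asks whether the four sources differ in any way. It treats the four texts alike, so a physician who does best, a politician who does worst or an influencer who comes last can each make it significant.

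Two things are at stake. A significant result from the named test is not evidence for prestige bias until the pattern behind it has been tested. And if the coefficients are then read without a stated rule, the reader cannot tell whether one, two or all three comparisons had to favour the influencer. The Project section says the researchers need no blinding when they analyse the results, so it is better to fix that rule beforehand.

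**Working it through.** **1. The article's own figure.** For one standard-normal predictor in logistic regression, the Wald formula with variance correction is n = (z_a·√v0 + z_b·√v1)² / (ln OR)².
- Inputs from Sample size: OR = 1.81, so ln OR = 0.5933 and its square is 0.3520; outcome probability 0.1; one-sided alpha 0.05 and power 0.95, so z_a = z_b = 1.645.
- By numerical integration, v0 = 10.016 and v1 = 11.221, with square roots 3.165 and 3.350.
- n = (1.645 × 6.515)² / 0.3520 = 326.16, rounded up to 327.

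The 327 reproduces exactly, as a one-sided test of a single continuous coefficient. The two-sided version of the same formula gives 390. The study was therefore sized neither for a 3-df comparison of four texts nor for three contrasts.

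**2. Form of the named test.** Four levels against a participant-only model give 4 − 1 = 3 degrees of freedom. Relabelling the texts leaves the statistic unchanged. If exactly one source is raised by a given odds ratio, the rejection rate is therefore the same whichever source it is. This follows from the form of the test and needs no simulation.

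**3. Illustration by simulation.** From the article: 327 / 4 ≈ 82 per text, seven binary items, OR 1.81, alpha 0.05. Assumed, because the article gives no values: baseline recall 10% or 50%, and a participant intercept SD of 0.5 to 1.5 on the logit scale. There were 10,000 runs per scenario. The 3-df comparison was approximated by a one-way F test on participant scores, and each contrast was tested at two-sided 0.05.

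| Baseline, SD | Influencer best: named test rejects | Influencer best: all three contrasts succeed | Influencer worst: named test rejects | Physician alone best: named test rejects |
|---|---|---|---|---|
| 10%, 1.0 | 74% | 54% | 58% | 74% |
| 10%, 1.5 | 50% | 29% | 39% | 51% |
| 50%, 0.5 | 99% | 96% | 99% | 99% |
| 50%, 1.0 | 86% | 64% | 85% | 86% |
| 50%, 1.5 | 58% | 32% | 57% | 57% |

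In the last two scenarios (influencer worst, physician alone best) all three contrasts succeed in 0% of runs. If the influencer ties with the physician and both exceed the other two, the named test rejects in 62% to 99.9% of runs and all three contrasts succeed in 2% to 4%. A second set of runs gave ranges within one point of those in the table.

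The rate for influencer worst is lower at 10% baseline because the same odds ratio moves the probability less downwards. For a participant with a random effect of zero, odds of 0.111 × 1.81 = 0.201 give 16.7% (up 6.7 points), while 0.111 / 1.81 = 0.061 gives 5.8% (down 4.2 points).

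Fitting the mixed model itself at 10% baseline with the influencer best (300 runs) gave 72% for the named test and 49% for all three contrasts at SD 1, and 89% and 74% at SD 0.5. Monte Carlo error on the 49% is about 1.96 × √(0.49 × 0.51 / 300) = 6 points.

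**4. Reading coefficients under no rule.** Take three contrasts that share the influencer as reference, with equal arms and no true difference. Some contrast is then significant at two-sided 0.05 about 12.6% of the time. At one-sided 0.05, the sidedness implied by z = 1.64, a false result in the influencer's favour occurs about 11.9% of the time. If the three were independent, the figure would be 1 − 0.95³ = 14.3%.

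**The case against.** The strongest reply is that the null-model comparison is offered as a check of model validity, not as the rule for accepting a hypothesis. The planned analysis is the regression, and its coefficients have signs. With the influencer as reference, they are exactly the three contrasts needed. The odds-ratio sizing with a one-sided z also suggests that the authors have coefficients in mind. Contrasts and multiplicity rules are often left to an analysis plan, which is not shown here.

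Much of this stands. A reader might infer that a significant chi-square is the article's decision rule and would be reported as support for prestige bias even with the influencer last. The article does not say so; it states no decision rule. A reader might also infer that the analysis cannot support the prediction. That goes too far, because the fitted model can. Nor should any single pair of power figures be read as the trial's own: baseline recall and participant SD are assumed, and the 0.1 under Sample size is an input to the software, not an expected recall rate. The four-person transmission chains were not simulated.

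What remains does not depend on silence. The article goes as far as naming a test, its function, its estimation method and its package, and that test is not matched to the predictions it prints.

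**Conclusion.** The point holds for the stated test taken alone. The article contains three inferential targets that do not agree: three directional comparisons in Hypotheses, a one-sided test of one normally distributed predictor in Sample size, and an undirected 3-df comparison in Data analysis. That mismatch rests on the text and on the form of the test, not on any assumed value.

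Its size can only be illustrated, for the recall stage and under the assumptions above. With the influencer best, the named test rejects in about 50% to 99% of runs and all three contrasts succeed in about 29% to 96%. With the influencer worst, the named test still rejects in about 39% to 99%. In the middle scenario (50% recall, SD 1) the rates are 86% with the influencer best and 85% with it worst, so the named test barely separates the prediction from its opposite. The 95% power claimed under Sample size is reached for the all-three claim only in the most favourable scenario examined. This is a correctable weakness in the stated inference, not a flaw in the model, data or design.

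**What to change.** In Data analysis, make the digital influencer the reference level and pre-specify three contrasts (against politician, physician and family member) as the test of each hypothesis. State the success rule and its sidedness. A rule that fits the predictions as worded is that all three odds ratios must favour the influencer, each at the 5% level; no multiplicity adjustment is needed because every contrast must pass. If claims against single comparators are wanted, apply Holm across the three. Other rules are defensible, provided one is chosen before the data are seen. Describe the null-model comparison as a global check.

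In Sample size, say which test the 327 supports, and give the power it provides for the chosen rule.

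The analysis change is wording only and needs no new data. The cost is lower power for the all-three claim than for the global test: in the mixed-model run at 10% recall and SD 1 (both assumed), 49% with two-sided contrasts or 61% with one-sided ones, against 72%. If that power is judged too low, the further cost is a larger sample.
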